## Abstract

**Background:**

Relisten is an artificial intelligence (AI)–based software developed by Recog Analytics that improves patient care by facilitating more natural interactions between health care professionals and patients. This tool extracts relevant information from recorded conversations, structuring it in the medical record, and sending it to the Health Information System after the professional’s approval. This approach allows professionals to focus on the patient without the need to perform clinical documentation tasks.

**Objective:**

This study aims to evaluate patient-reported satisfaction and perceived quality of care, assess health care professionals’ satisfaction with the care provided, and measure the time spent on entering records into the electronic medical record using this AI-powered solution.

**Methods:**

This proof-of-concept (PoC) study is conducted as a multicenter trial with the participation of several health care professionals (nurses and physicians) in primary care centers (CAPs). The key outcome measures include (1) patient-reported quality of care (evaluated through anonymous surveys), (2) health care professionals’ satisfaction with the care provided (assessed through surveys and structured interviews), and (3) time saved on clinical documentation (determined by comparing the time spent manually writing notes versus reviewing and correcting AI-generated notes). Statistical analyses will be performed for each objective, using independent sample comparison tests according to normality evaluated with the Kolmogorov-Smirnov test and Lilliefors correction. Stratified statistical tests will also be performed to consider the variance between professionals.

**Results:**

The protocol has been developed using the SPIRIT (Standard Protocol Items: Recommendations for Interventional Trials) checklist. Recruitment began in July 2024, and as of November 2024, a total of 318 patients have been enrolled. Recruitment is expected to be completed by March 2025. Data analysis will take place between April and May 2025, with results expected to be published in June 2025.

**Conclusions:**

We expect an improvement in the perceived quality of care reported by patients and a significant reduction in the time spent taking clinical notes, with a saving of at least 30 seconds per visit. Although a high quality of the notes generated is expected, it is uncertain whether a significant improvement over the control group, which is already expected to have high-quality notes, will be demonstrated.

**Trial Registration:**

ClinicalTrials.gov NCT06618092; https://clinicaltrials.gov/study/NCT06618092

**International Registered Report Identifier (IRRID):**

DERR1-10.2196/66232

## Introduction

### Background

In the medical field, medical record writing is an essential task that requires time and accuracy on the part of health care professionals. The medical record, which includes the patient’s medical history, any symptoms they have had, treatments performed, and other relevant details, is a critical component in making appropriate medical decisions and ongoing patient follow-up [1].

In the modern health care context, there has been a transition to the digitization of these records, giving rise to the concept of the electronic medical record (EMR). An EMR is the electronic representation of a patient’s medical record, created and maintained by health care professionals. This digital approach has not only revolutionized the way medical information is stored and accessed but has also improved the efficiency of medical care by facilitating the retrieval of relevant data at the point of care [2,3]. EMRs provide a centralized platform for medical information management, allowing for more accurate tracking and more coordinated care [4].

Traditionally, health care professionals have spent a significant amount of time writing medical records [5], which can affect the efficiency and quality of care they provide. This manual task is not only time-consuming but can also lead to documentation errors, omissions, or inconsistencies in the information recorded. A descriptive study published in the *Annals of Internal Medicine* in 2020 conducted a detailed assessment of the amount of time doctors spent using EMRs during outpatient visits. In this study, which included comparisons of 1482 doctors, it was found that doctors were actively using EMRs for 43% of the total time they were online [6]. It has also been shown that all this can contribute to an increase in burnout among professionals [7,8].

In recent years, the field of artificial intelligence (AI) has experienced significant advances in natural language processing and speech recognition [9,10]. These advances have enabled the creation of automated tools and systems that can accurately and efficiently transform speech into text. In the health care setting, this technology has the potential to streamline and improve the writing of medical records, freeing up time for professionals to focus on direct patient care [11,12]. However, this technology was necessary but not sufficient, and it was not until the advent of generative AI that a key part of the process could be completed to obtain sufficient quality for practical use [13,14].

Another important aspect is the issue of data privacy and security [15]. The implementation of AI systems in clinical practice must comply with strict regulations regarding the protection of patient health data. This includes ensuring the security of data transmission and storage, as well as compliance with data privacy regulations, and the General Data Protection Regulation [16]. In the case of AI use, these requirements must go further, given the additional risks of training models with data in health care, which in the worst cases can result in data hacking or the inclusion of strong biases in the algorithms [17,18].

Several companies and academic institutions have developed prototypes and pilot systems for the automated writing of medical records from the doctor-patient conversation in English (Nuance DAX, Amazon HealthScribe). These tools use advanced algorithms and AI models trained on large amounts of clinical data to extract and record relevant information [19].

### Relisten

In this context, the Spanish company Recog Analytics has developed Relisten [20], an automated clinical note-writing system designed to handle real-world consultations, supporting multiple languages and offering integration with EMRs.

Through a natural conversation between the health care professional and the patient, this AI-powered tool uses recordings to extract relevant fields corresponding to key sections of the medical history in a structured way and then send them to the Health Information System (after correction and approval by the health care professional). A detailed description of the algorithm’s architecture can be found in Multimedia Appendix 1, providing technical insights into its design and functionality.

## Methods

### Study Objectives

This study has the following objectives: (1) to evaluate the perceived quality of care reported by patients with the use of an AI-powered solution in the consultation, measured through anonymous satisfaction questionnaires at the end of each consultation (Multimedia Appendix 2); (2) to assess the satisfaction of health care personnel with the care provided in consultations, measured using an anonymous satisfaction survey at the end of the study (Multimedia Appendix 3) and a structured interview; and (3) to assess the time spent by health care personnel on entering records in the EMR, measured by statistical tests comparing consultations with and without the tool.

### Overview, Design, and Hypotheses of Study

A proof-of-concept (PoC) analysis will be carried out in the context of a multicenter study, where several health professionals (nurses and physicians) from different primary care centers (CAPs) will use the AI-powered tool in consultations (under informed consent of the patient) and will survey patients and the professionals themselves.

The project is structured in three main phases: (1) preparation: this includes the demonstration and initial training of the participating professionals, the preparation of the technological infrastructure (microphones), and the coordination for carrying out the surveys, with an approximate duration of 2 weeks; (2) development: this consists of the use of an AI-powered solution during consultations, as well as data collection, including audios, clinical notes, and survey results, lasting approximately 20 weeks; and (3) data analysis and presentation of results: this phase involves the processing and analysis of the data collected, followed by the presentation of the results obtained, and lasts approximately 2 weeks.

The measurement of the objectives will be carried out using the following methods: (1) perceived quality of care as reported by patients using an anonymous patient survey after each consultation, in a patient-blinded study (patients are not told beforehand whether the AI-powered tool has been used in the consultation; this fact is outlined by a graphic mark in the surveys in which the tool has been used); (2) satisfaction of health care personnel: an anonymous survey will be conducted at the end of the study. This will qualitatively evaluate the tool’s impact on consultations, focusing on aspects such as its general usefulness, ease of use, the quality of notes generated, its perceived ability to improve attention during consultations, and the extent to which it saves time. In addition, the study will incorporate structured interviews with primary care health care professionals (nurses and physicians) to explore their experiences with the tool in depth. The interviews will include questions about the above concepts, as well as at least an additional request to the health care professional to identify limitations and improvements to the tool. (3) Time spent entering information into the EMR. To determine the magnitude of savings, 2 measurements taken during the PoC will be compared: the time the health care professional spends typing in the consultation and the time the health care professional spends reviewing and correcting notes generated by the AI-powered tool.

Figure 1 facilitates the visualization of the development of the study in consultations.

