### Data Collection

The data collection process involves the following:

Satisfaction surveys completed by patients at the end of the consultation (with the AI-powered tool as a test and without the tool as a control). The survey will be given to the patient on paper by the health professional inside the doctor’s office at the end of the visit. They will be collected anonymously in a box upon exiting the office, in a visible and accessible place. This involves single-blinded data collection (the patient does not know whether the AI-powered tool is being used, although the health care professional does). These questionnaires will be available in Catalan and Spanish.Quality surveys at the end of each consultation by health care professionals, on a scale of 0-10 with the possibility of including open-ended comments, will be carried out directly through the AI-powered tool’s digital platform. These questionnaires will be available in Catalan and Spanish.Satisfaction surveys completed by health care professionals at the end of the study, as well as interviews to better understand the impact and limitations in a qualitative manner.Recordings of conversations between the patient and health care professional (Recog will delete the recordings at the end of the study).

These items align with study objectives and are detailed in the Multimedia Appendices 2 and 3.

Qualitative data will be collected using open-ended survey surveys for patients and health care professionals and structured interviews with professionals. These data will be analyzed using thematic analysis.

The study variables are mentioned in Textbox 1.

Study variables.

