## Results

This study was preregistered on ClinicalTrials.org. Recruitment began in July 2024, and as of November 2024, a total of 318 patients have been enrolled at participating CAPs. The recruitment process is proceeding more slowly than expected and to ensure sufficient sample size the recruitment period has been extended until March 2025. This adjustment enables comprehensive data collection without compromising the study’s objectives.

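### Professional satisfaction is surveyed once, at the end of a period extended from about 20 to 30–39 weeks, so the result may over-represent professionals who kept using the tool

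*Protocol article*

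**What the plan says.** The timing of the professional satisfaction survey is stated three times in the protocol article, each time the same way. Study Objectives says of objective 2 that it is "measured using an anonymous satisfaction survey at the end of the study (Multimedia Appendix 3) and a structured interview". Overview, Design, and Hypotheses of Study says "satisfaction of health care personnel: an anonymous survey will be conducted at the end of the study". Data Collection lists "Satisfaction surveys completed by health care professionals at the end of the study, as well as interviews". No baseline or interim survey is described.

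The interviews are described as "structured interviews with primary care health care professionals (nurses and physicians) to explore their experiences with the tool in depth". They have no date of their own; Data Collection simply lists them next to the end-of-study survey.

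There is one repeated instrument: "Quality surveys at the end of each consultation by health care professionals, on a scale of 0-10 with the possibility of including open-ended comments". The description of the workflow steps under Figure 1 presents this as a rating of the notes that the tool produced for that consultation.

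On duration, Overview, Design, and Hypotheses of Study plans a development phase of tool use and "data collection, including audios, clinical notes, and survey results, lasting approximately 20 weeks". Results reports a July 2024 start, 318 patients enrolled as of November 2024, and slower recruitment than expected, so that "the recruitment period has been extended until March 2025".

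**The concern.** The end of the study is set by patient accrual, not by how long each professional has worked with the tool. When accrual slowed, the survey date moved with it and the survey rule stayed as it was. The longer the interval, the more likely it is that a professional who gives up the tool is asked long afterwards, answers from memory, or does not answer.

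This would not matter if stopping had nothing to do with satisfaction. But the survey asks about usefulness, ease of use, note quality and time saved, and dissatisfaction with any of these is a plausible reason to stop. A survey timed only at study end could then select respondents partly on the outcome it measures. The interviews, if held at the same time, could also under-represent people who ran into the limitations they are meant to uncover. At stake is whether objective 2 describes all professionals who took part or mainly those who carried on.

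**Working it through.** **1. Length of the period.** Inputs: July 2024 and March 2025 (Results) and about 20 weeks (Overview, Design, and Hypotheses of Study). The 20 weeks is a planned value, so there is no calculation to reproduce. It does fit the calendar: 20 weeks from 1 July 2024 is 18 November, and from 31 July it is 18 December, in line with a November status report followed by an extension.

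- Shortest reading, 31 July 2024 to 1 March 2025: 213 days / 7 = 30.4 weeks, or 30.4 / 20 = 1.52 times the plan.
- Longest reading, 1 July 2024 to 31 March 2025: 273 days / 7 = 39.0 weeks, or 39.0 / 20 = 1.95 times the plan.

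Accrual as of November was 318 / 800 = 39.8% of target.

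**2. Delay for someone who stops early.** Take, as an illustration only, a professional who starts at the beginning, stops after 8 weeks and is surveyed when recruitment closes.

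- Planned: 20 − 8 = 12 weeks after last use.
- Extended: 30.4 − 8 = 22.4 weeks to 39.0 − 8 = 31.0 weeks after last use.

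The delay roughly doubles or more, with no change in the survey text.

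**3. What the other instruments cover.**

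| Instrument | Timing | Content | Reaches early leavers? |
|---|---|---|---|
| Satisfaction survey | Once, study end | Usefulness, ease of use, note quality, attention, time saved | Late, or perhaps not |
| Structured interview | No date of its own | Same themes plus limitations | Not stated |
| 0-10 rating with comments | Each consultation | Generated notes | Yes, up to last use |

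The repeated rating therefore covers note quality only. Optional comments may catch more, but not systematically.

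**4. Possible size.** Let S be the mean among those surveyed, f the share of starters not surveyed, and D how much lower those people would have scored.

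Mean over all starters = (1 − f)·S + f·(S − D) = S − f·D, so the survey is too high by f·D.

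The article gives neither the number of professionals nor any stopping rate, so f and D are assumptions. A 1–5 scale is assumed too, following the study variables in Textbox 1.

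| f | D = 0 | D = 0.5 | D = 1.0 | D = 1.5 |
|---|---|---|---|---|
| 0 | 0 | 0 | 0 | 0 |
| 0.10 | 0 | 0.05 | 0.10 | 0.15 |
| 0.20 | 0 | 0.10 | 0.20 | 0.30 |
| 0.30 | 0 | 0.15 | 0.30 | 0.45 |

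The range is 0 to 0.45 points. If nobody is lost, or if those lost would have scored the same, the bias is zero.

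**The case against.** The strongest reply is that nothing in the article shows a problem has occurred. No professional is reported to have stopped. The survey is addressed to participating health care professionals generally, not to current users, and someone who stops using the software may still work at the same center and be easy to reach. The extension concerns recruitment; it does not say that any individual uses the tool throughout. The full protocol, which is not shown, may say how withdrawals are handled. A survey at study end is also an ordinary choice for a proof of concept, and objective 2 is not one of the two objectives that were sized.

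Most of this stands, and it rules out several stronger readings. A reader might infer that early leavers are in fact missed and that the result does favour those who stayed; the article supports only the possibility. A reader might infer that professionals' views are gathered only once; the rating after each consultation and the undated interviews contradict that. A reader might infer that those who stop could never be identified because the survey is anonymous. Textbox 1, however, lists a stored user code for each professional, so the team can count who stopped contributing. What anonymity prevents is linking a survey answer to a code.

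The objection does not remove the timing itself. It is a stated rule, repeated in three sections, and the extension has stretched its consequence. If the full protocol already surveys professionals when they stop, these three sections do not say so and should be aligned with it. The rating of notes does not replace a survey on ease of use, attention and time saved.

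**Conclusion.** The point holds as a design risk that is cheap to remove, not as a demonstrated bias. What is certain is the single end-of-study survey and the lengthening of the period by a factor of about 1.5 to 1.95. What is conditional is the effect: it needs some professionals to stop early, some of those not to respond or to answer differently after a long gap, and their satisfaction to be lower. None of these is documented. The 0 to 0.45 points quantifies only non-response among leavers and rests wholly on the assumed ranges for f and D. It should not be judged against the 0.25-point difference in Sample Size and Randomization, because that figure belongs to the patient survey.

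**What to change.** In Study Objectives, in Overview, Design, and Hypotheses of Study, and in Data Collection, change the timing so that the survey and interview are offered when each professional stops using the tool or at study end, whichever comes first, to everyone who used it at least once. Anyone who has already stopped when the change is made can be given the form then.

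Report the number of responses out of all professionals who started, and the number who stopped early, counted from the stored user codes. Neither count requires linking an answer to a person.

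A box on the form marking early stopping would let the two groups be described separately. It should be optional, and used only if the group is large enough to keep answers anonymous; the article does not give the number of professionals.

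The cost is small: the same form and interview guide, given earlier to however many people stop. The one drawback is that early leavers report on a shorter experience, which the report should say.

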### Setting of the Study

The study population will be made up of patients who are visited in person at CAPs in Catalonia, both in emergency and control consultations, whose professionals (nurses and physicians) participate in the study. The participating primary care centers are CAP Amposta, CAP Centelles, CAP Artés, CAP Sallent, CAP Súria, and the Consorci d’Atenció Primària de Salut Barcelona Esquerra.

Given the nature of the tool and its applicability to most of the practice settings, there will be no previous selection of patients, but any patient who comes for consultation with the professionals participating in the study will be eligible.

Participants eligible for inclusion in the study must have provided written informed consent, be involved in face-to-face medical or nursing consultations conducted in Catalan or Spanish, and be aged 18 years or older.

Participants will be excluded from the study if they are unable to understand the nature of the study, lack fluency in Catalan or Spanish, do not provide consent to be recorded, or if any technical issues, such as internet service downtime, compromise the recording process.

The study included patients in unscheduled visits (emergency), first visits (with history taking), and follow-up for chronic disease.

The SPIRIT guidelines were followed when designing the research (Multimedia Appendix 4) [21].

### Sample Size and Randomization

To calculate the sample size, the 2 objectives that require such calculation are considered:

For the patient satisfaction surveys, proposed on a Likert scale from 1 to 5, we are faced with the problem of comparing independent samples. Assuming normality in the difference of the samples (a hypothesis that will be verified during the statistical tests), the formula for the determination of the required sample size is the following:

Where Z_α_ and Z_β_ represent the Z-table values for confidence level and test power, respectively, sigma is the SD of the (estimated) differences, and d is the effect size to be measured. For this study, standard values for α=.05 (95% confidence) and β=.8 (80% test strength) are selected, σ=1 is estimated as an extreme case to ensure that the results will be statistically significant, and d=0.25, as the minimum improvement we want to demonstrate. The result is n=395.21 for each group, so we set the number of patients to be analyzed to 400 with the AI-powered tool and 400 without the tool.For time-saving, applying a similar procedure with the same standard values, σ=90 seconds and d=30 seconds, we obtain n=111.15 for each group, so we set the number of consultations to be analyzed to 120 with the AI-powered tool and 120 without the tool.Since the groups are the same and there is no interconnection between the measurement of both objectives, it is possible to use the same consultations for both, and therefore the total number of patients required will be the larger of the two above, resulting in n=800 (400 patients with the AI-powered tool and 400 without the tool).The randomization was carried out in a simple format, given the sufficient sample size and the fact that the aim is to validate the hypotheses at a general level, although for information purposes the study also shows intermediate results stratified by type of consultation (first or follow-up) or by a health professional.

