### Statistical Analysis

The main hypotheses of the study focus on evaluating the reported quality of care and saving time in the writing of clinical notes. To assess the improvement in reported quality of care, the normality of the sample will be checked using the Kolmogorov-Smirnov test with Lilliefors correction. Student *t* test for independent samples will be applied in the case of normality, or an equivalent nonparametric test otherwise. Key survey items, including patient-reported satisfaction with time spent, the attention received, and perceived care quality, as well as health care professional satisfaction with reduced administrative burden, ease of use, and note quality, will be analyzed to test for significant differences.

In terms of time savings, 2 aspects will be measured separately: the relative time (in percentage) that the professional spends writing notes during the consultation without using the AI-powered solution, and the relative time that the doctor spends reviewing the notes generated by the tool. Similarly, the normality of the sample will be checked using the Kolmogorov-Smirnov test with Lilliefors correction, and the Student *t* test or its nonparametric equivalent will be applied as appropriate.

Since the sample is not randomized, a sensitivity analysis will be conducted to account for potential selection bias. All statistical analyses will be performed using RStudio, considering a confidence level of 95% and a statistical power of 80%.

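### The two sample sizes come from different multipliers and an undeclared one-sided alpha: 400 per group is more than satisfaction needs, and 120 per group for time reaches 80% power only if the test is one-sided

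*Protocol article*

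**What the plan says.** The section Sample Size and Randomization of the protocol article sizes the study on two objectives, each a comparison of independent groups.

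- Common settings: "standard values for α=.05 (95% confidence) and β=.8 (80% test strength) are selected". Sigma is described as the SD of the estimated differences.
- Satisfaction, on a 1 to 5 scale: sigma is 1, and "d=0.25, as the minimum improvement we want to demonstrate". Then: "The result is n=395.21 for each group, so we set the number of patients to be analyzed to 400 with the AI-powered tool", with the same number without the tool.
- Time: "applying a similar procedure with the same standard values", with sigma 90 seconds and d 30 seconds. Then: "we obtain n=111.15 for each group, so we set the number of consultations to be analyzed to 120 with the AI-powered tool", again with the same number without the tool.
- The same consultations may serve both objectives, so the larger size governs and the total is 800.

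The section Statistical Analysis plans this comparison: "Student *t* test for independent samples will be applied in the case of normality, or an equivalent nonparametric test otherwise". All analyses are run "considering a confidence level of 95% and a statistical power of 80" per cent. Neither section says whether the tests are one-sided or two-sided. The Results section reports slow recruitment, and "to ensure sufficient sample size the recruitment period has been extended until March 2025".

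**The concern.** With the same alpha and power, two sample sizes from one formula can differ only through (sigma/d)². That ratio does not hold here, so at least one of the two per-group figures is not what its label says. The satisfaction figure is the one that sets the size of the trial, and the recruitment period has been lengthened to secure that size.

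The sidedness is a second matter. The stated sizes can be recovered only with the one-sided 5% value, while the text speaks only of 95% confidence and of testing for differences. Someone who runs the default two-sided test would have a different power for time from the one the article claims.

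Third, calling sigma an SD of differences fits a paired design, whereas both comparisons are between independent groups.

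**Working it through.** **Inputs**, all from Sample Size and Randomization: alpha 0.05; power 80% (written there as beta = .8); satisfaction sigma 1 and d 0.25, so (sigma/d)² = 16; time sigma 90 s and d 30 s, so (sigma/d)² = 9.

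**Check that needs no formula.** With common alpha and power, the sizes should stand in the ratio 16/9 = 1.778. The stated ratio is 395.21/111.15 = 3.556, exactly twice that.

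**Reproducing the stated figures.** With rounded one-sided values, (1.645 + 0.84)² = 6.1752.

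- Satisfaction: 4 × 6.1752 × 16 = 395.21.
- Time: 2 × 6.1752 × 9 = 111.15.

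Both match to two decimals. The multiplier is 4 in one and 2 in the other. Multipliers 1, 2 and 4 were tried with one- and two-sided alpha; no single choice gives both figures. Multiplier 2 for satisfaction would give 197.61, and multiplier 4 for time would give 222.31.

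**One formula for both.** For two independent groups of equal size, n per group = 2(z_alpha + z_beta)² sigma²/d², with z_alpha/2 in place of z_alpha for a two-sided test and sigma the SD of individual values. With unrounded normal values the squared sum is 6.1826 one-sided and 7.8489 two-sided.

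| Objective | One-sided 5% | Two-sided 5% | Stated |
|---|---|---|---|
| Satisfaction | 2 × 6.1826 × 16 = 197.8, so 198 | 2 × 7.8489 × 16 = 251.2, so 252 | 395.21, set to 400 |
| Time | 2 × 6.1826 × 9 = 111.3, so 112 | 2 × 7.8489 × 9 = 141.3, so 142 | 111.15, set to 120 |

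**Power of the stated sizes.** Power = Φ(d/(sigma√(2/n)) − z).

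- Satisfaction, 400 per group: 0.25/√(2/400) = 3.536. One-sided Φ(3.536 − 1.645) = 97.1%; two-sided Φ(3.536 − 1.960) = 94.2%. The difference detectable with 80% power, two-sided, is (1.960 + 0.8416) × √(2/400) = 0.198 points.
- Time, 120 per group: 30/(90√(2/120)) = 2.582. One-sided Φ(0.937) = 82.6%; two-sided Φ(0.622) = 73.3%. By the t distribution these are 82.4% and 73.0%. The two-sided difference detectable with 80% power is 2.8016 × 11.62 = 32.6 s.
- Time, if every consultation is timed, 400 per group: 30/(90√(2/400)) = 4.714, giving 99.9% one-sided and 99.7% two-sided. Even 252 per group would give 96.3% two-sided.

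**The case against.** **The time figure can be defended.** At the one-sided 5% value that was used, 111.15 is the correct per-group result and 120 exceeds 80% power. Several cues are directional: the symbol is Z_α, the satisfaction difference is framed as an improvement to be shown, the hypothesis is that the tool improves perceived quality, and the abstract expects a saving of at least 30 seconds. A reader might infer that 120 per group simply misses 80% power. The documents do not support that. The shortfall needs two conditions: a two-sided test, and timing that stops at 120 per group. The article allows the same consultations to be used for both objectives, and its workflow records typing or review time in each arm. What stands is that the sidedness is not declared, and that the stated number to be analysed for time is 120.

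**The factor of 4 may have another source.** It also arises as 2 × (√2)², if sigma was turned into the SD of a difference between two individuals. That SD has variance 2 sigma², which the multiplier 2 already covers, so this would count it twice; and the time figure does not do it. The figure equals a two-group total under the one-sided formula, but how it arose cannot be proved. The displayed formula was not visible in the text reviewed; whatever it shows, it cannot give both results from the same alpha and power. The inconsistency stands.

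**The error is on the safe side.** An overlarge satisfaction sample puts no conclusion at risk. This is correct, and it lowers the severity.

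**Conclusion.** The point holds. The two per-group sizes use multipliers 4 and 2, and both rest on an undeclared one-sided 5% alpha. On the article's own inputs, satisfaction needs 198 per group (one-sided) or 252 (two-sided), so 400 per group is overstated under either reading and delivers about 97% or 94% power. For time, 120 per group gives about 82% one-sided and 73% two-sided. The latter would call for 142, a gap that vanishes if all planned consultations are timed.

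A reader might go on to infer that recruitment could end once 2 × 252 = 504 surveys are in. The documents do not support that. The 252 assumes a t test, complete data and the stated sigma. The Statistical Analysis section allows a nonparametric test; at the usual efficiency of 3/π under normality (an assumption here), the two-sided sizes rise to about 264 for satisfaction and 148 for time. The limitations section foresees excluding extreme values. Time is also to be analysed as a percentage although it was sized in seconds, so 142 does not by itself establish power for that analysis. Projecting accrual from the 318 patients reported in November 2024 to March 2025, at a constant rate over an assumed 3.5 to 5 months, gives about 570 to 770. This is illustrative only.

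Severity: should be fixed. The certain error is conservative; the possible loss of power for time is conditional and easily avoided.

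**What to change.** 1. State whether each test is one-sided or two-sided, in both the sample-size and the analysis sections.
2. Give one formula for both objectives, n per group = 2(z_alpha or z_alpha/2 + z_beta)² sigma²/d², and define sigma as the SD of individual scores or times.
3. Restate the required sizes: 198 and 112 per group if one-sided, 252 and 142 if two-sided. State what 400 per group delivers for d = 0.25: 97% or 94%.
4. Say how many consultations will be timed. If the test is two-sided, time at least 142 per arm, and preferably all of them.
5. If the total falls short of 800, report the power for the number actually analysed, allowing for the nonparametric test and for exclusions, rather than declaring a fixed smaller number sufficient.

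The cost is a text correction. In the two-sided case, add the timing of at least 142 − 120 = 22 more recordings per arm, from consultations already planned. No extra patients are needed, and because only design inputs are used, the change can be made before any outcome data are examined.
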